## Abstract

**Background:**

With the increased understanding of heart disease, microvascular angina (MVA) is receiving greater attention from clinicians. Studies have shown that patients with MVA have significantly higher major cardiovascular events and all-cause mortality than the control population, and the search for effective treatments is of great clinical importance. Both basic and clinical studies have shown that Qi-Jing Hui-Xin Decoction (QJHX) can relieve angina symptoms and improve clinical efficacy, but there is a lack of high-quality clinical studies to provide a research basis. This article introduces the evaluation protocol of QJHX for the adjunctive treatment of MVA.

**Methods/design:**

This is a prospective randomized controlled trial. The trial will enroll 150 patients with MVA. On the basis of Western drug treatment, patients will be randomized into two groups, and the experimental group will receive QJHX treatment for 12 weeks and follow-up at 24 week. The primary indicators are the clinical efficacy of angina pectoris and the evidence of traditional Chinese medicine (TCM) efficacy. Secondary indicators are the Seattle Angina Scale score, serum lipid levels, electrocardiogram, and echocardiogram diagnosis. Additional indicators are endothelial function and immunoinflammatory factors. Adverse events will be monitored throughout the trial.

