### Sample size

According to the results of a previous single-center clinical observation, after 12 weeks of treatment with QJHX, the effective rate was 85.7% in the treatment group and 60.1% in the control group. According to the sample calculation decoction, the number of samples is *n* = 61 cases in each group. In the decoction, *p*_*1*_ and *p*_*2*_ are the estimated values of the two population rates, respectively, *p* is the combined rate, *p* = (*p*_*1*_ + *p*_*2*_)/2, when *α* = 0.05, *β* = 0.10, *u*_α_ = 1.96, and *u*_β_ = 1.282 in the double test and bilateral test. The sample size was 75 cases in each group, a total of 150 cases, taking into account a 20% drop-off rate.
$$ {\mathrm{n}}_1={n}_2{\frac{\left[ ua\sqrt{2p\left(1-p\right)}+ u\beta \sqrt{p_1\left(1-{p}_1\right)+{p}_2\left(1-{p}_2\right)}\right]}{{\left({p}_1-{p}_2\right)}^2}}^2 $$

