### Randomization and concealment

Eligible patients will be randomly assigned to the treatment group or the control group in a 1:1 ratio, using SAS® 9.4 statistical software and a site-stratified, block randomization schedule. Randomized allocation sequence of the trial participants will be sealed in opaque envelopes and kept in a double-locked cabinet in an independent data center. Each participating hospital will have an independent drug administrator responsible for random coding and drug management.

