### Outcomes

The primary outcome is Angina Scale and TCM syndrome score according to the guiding principles of clinical research technology of traditional Chinese medicine and natural medicine in the treatment of coronary heart disease and angina pectoris. The higher the score, the more severe angina pectoris and symptoms. The secondary outcomes are based on the Seattle Angina Questionnaire (SAQ), another scale of angina; three scales will be collected at baseline, 4, 8, and 12 weeks after randomization. Serum total cholesterol [13], triglyceride [14], high-density lipoprotein cholesterol (HDL-C), low-density lipoprotein cholesterol (LDL-C), non-high-density lipoprotein cholesterol (non-HDL-C), apolipoprotein [8] A-I, ApoA-II, ApoB, lipoprotein-a, and the proportions of related biochemical parameters, including TC/HDL-C, non-HDL-C/HDL-C, and ApoB/Apo A-1, endothelin (ET), nitric oxide (NO), prostaglandin E (PGE), calcitonin gene-related peptide (CGRP), hypersensitive-C-reactive-protein (hs-CRP), and tumor necrosis factor α (TNF-α); the results of transthoracic Doppler echocardiography (TTDE), including left ventricular end-diastolic diameter (LVEDD), left ventricular end-systolic diameter (LVESD), left atrium (LA), interventricular septal thickness (IVST), left ventricular posterior wall (LVPW), fractional shortening (FS), and left ventricular ejection fraction (LVEF); an electrocardiogram (EKG) will be measured and collected at baseline and 12 weeks after randomization.

Safety outcomes are blood routine examination and laboratory liver and renal function test results, including aspartate aminotransferase (AST), alanine aminotransferase (ALT), alkaline phosphatase (ALP), blood urea nitrogen (BUN), creatinine (CR), and uric acid (UA). Adverse events will be monitored at each visit. The investigators will evaluate the degree of adverse events and whether they are related to the intervention, and they will ensure that the adverse events are properly resolved. All collected adverse events and subsequent medical intervention will be recorded in the CRF.

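### Two unranked primary outcomes share a sample size calculated for a single test, so the stated 5% error and 90% power do not describe success until a success rule is fixed

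*Protocol article*

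**What the plan says.** Two places in the protocol article name a pair of primary outcomes. The abstract (Methods/design) has: "The primary indicators are the clinical efficacy of angina pectoris and the evidence of traditional Chinese medicine (TCM) efficacy". The Outcomes section has: "The primary outcome is Angina Scale and TCM syndrome score". Neither ranks the two or says whether success needs one or both. The Outcomes section collects the scales at baseline and at weeks 4, 8 and 12.

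The Sample size section uses one pair of 12-week rates from an earlier single-centre observation: "the effective rate was 85.7% in the treatment group and 60.1% in the control group". It does not say whether these rates concern angina or TCM syndrome. The calculation is run "when *α* = 0.05, *β* = 0.10", two-sided, and gives "61 cases in each group", raised to 75 per arm (150 in total) for 20% drop-off.

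The Statistical analysis section lists ordinary two-group tests (t tests, Mann-Whitney, chi-square, Fisher's exact). It gives no significance level and no rule for combining the two primary outcomes. The Recruitment section plans an intention-to-treat analysis with last observation carried forward for discontinuers.

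**The concern.** A sample size calculated for one comparison guarantees its alpha and power for that comparison only. With two primary outcomes, those figures carry over to the trial's conclusion only if a rule links the outcomes. The two simplest rules each break one of them. If either outcome is enough at 0.05, there are two chances of a false positive. If both must be significant, there are two chances of a miss.

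The practical risk is a trial reported as positive on the TCM syndrome score alone while angina is unmoved, with the 5% error rate of the sample size section taken to apply. The Interventions section gives the control group primary treatment only and describes no placebo, so a claim resting on one symptom-based score deserves a firm rule.

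**Working it through.** **Inputs from the protocol article:** p1 = 0.857, p2 = 0.601, two-sided alpha 0.05 (u = 1.96), beta 0.10 (u = 1.282), 1:1 allocation, 61 evaluable per arm, 75 randomised per arm.

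**Assumed, because not given:** the correlation ρ between the two test statistics (range 0 to 0.9), and an effect on the second outcome equal to that on the first.

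**1. The plan's own figure.** Pooled rate p = (0.857 + 0.601)/2 = 0.729.

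- √[2p(1−p)] = √0.3951 = 0.6286
- √[p1(1−p1) + p2(1−p2)] = √(0.1226 + 0.2398) = 0.6020
- n = (1.96 × 0.6286 + 1.282 × 0.6020)² / 0.256² = 2.0037² / 0.06554 = 61.26

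The stated 61 is reproduced (62 if rounded up). So 61 per arm is the size for one test of one rate.

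**2. Power of one test at 61 per arm.** (0.256 × √61 − 1.96 × 0.6286)/0.6020 = 1.275, and Φ(1.275) = 0.8988, or 89.9%. At 75 per arm the same formula gives 1.636 and 94.9%.

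**3. Either outcome suffices, each at 0.05.** Familywise error = 1 − P(|Z1| < 1.96, |Z2| < 1.96) for a bivariate normal with correlation ρ. At ρ = 0 this is 1 − 0.95² = 9.75%.

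**4. Both required, each at 0.05.** Joint power = P(Z1 < m, Z2 < m), with m = 1.275 at 61 per arm and 1.636 at 75 per arm. At ρ = 0 and 61 per arm this is 0.8988² = 80.8%. Under this rule the type I error stays at or below 5%.

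| Assumed ρ | Familywise error, either suffices | Joint power, both required, 61 per arm | Joint power, both required, 75 per arm |
|---|---|---|---|
| 0 | 9.75% | 80.79% | 90.08% |
| 0.3 | 9.51% | 81.97% | 90.56% |
| 0.5 | 9.07% | 83.06% | 91.07% |
| 0.8 | 7.81% | 85.47% | 92.35% |
| 0.9 | 7.04% | 86.74% | 93.07% |

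**5. Alpha split, 0.025 each.** At 61 per arm the power per outcome is 83.7%. The chance of winning at least one, if the outcomes are independent and equally affected, is 1 − (1 − 0.837)² = 97.3%, with familywise error at or below 5%.

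**The case against.** The strongest reply is that the article is silent on the rule and does not fix a wrong one. Ordering and alpha allocation are commonly left to the statistical analysis plan, which is not shown, and some rules do work at 150 patients. A fixed sequence keeps 5% error and about 90% power for the first outcome. A split alpha keeps 5% error and, under the assumptions in step 5, gives about 97% power to win at least one. This stands. A reader might infer that the trial must either exceed 5% error or fall below 90% power, and the document does not support that. What remains is that the protocol itself declares two primary outcomes and fixes the sample size for one unnamed rate. A later plan can choose a rule, but at 61 evaluable per arm it cannot bring a both-required rule to 90% power over the correlations examined.

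The second reply is that last observation carried forward may put all 75 per arm into the analysis, giving joint power of about 90% or more. The arithmetic is right. It uses up the whole drop-off allowance and assumes that discontinuers carry the full 12-week effect, which is optimistic.

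Three further inferences go beyond the text:

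- A reader might say that the analysis section tests everything at an unadjusted level. It states no level at all; 0.05 appears only under Sample size.
- A reader might count weeks 4, 8 and 12 on both scales as six primary tests, for an error of 1 − 0.95⁶ = 26.5%. Weeks 4 and 8 are not called primary, the sizing refers to 12 weeks, and repeated readings in the same patients are not independent.
- A reader might take the 90% power to be for angina. The rates are not tied to angina.

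Finally, the Discussion calls the trial preliminary. That lowers the stakes, but the abstract promises high-level evidence, and the trial is sized with formal alpha and power.

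**Conclusion.** The point holds in a limited form. Two unranked primary outcomes are paired with a calculation for one unnamed rate, so the stated alpha and power belong to a single test that the protocol has not identified.

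- If either outcome suffices at 0.05, the familywise error is up to 9.75%, and 7.0% at a correlation of 0.9.
- If both are required, joint power at 61 evaluable per arm is about 81%, rising to 87% at a correlation of 0.9.

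The error figures rest on the assumed correlation. The power figures also rest on an assumed equal effect on the second outcome. The document does not show that the trial is too small or that its error rate is bound to exceed 5%: a suitable rule, stated in time, avoids both.

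**What to change.** Before any unblinded analysis:

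1. State which outcome the 85.7% and 60.1% rates belong to.
2. Name that outcome at week 12 as the single primary (angina, if the rates are for angina), in the form that those rates measure, tested at two-sided 0.05.
3. Name the other outcome at week 12 as key secondary, tested at two-sided 0.05 only if the first is significant.
4. Align the abstract, Outcomes, Sample size and Statistical analysis sections with this.

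This holds the error at 5% over the two outcomes and keeps about 90% power for the first. The cost is one paragraph and no extra patients. The downside is that no confirmatory claim on the second outcome is possible if the first fails. The chance of winning both is still the joint power in the table.

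If the sponsor does want both outcomes to be required, 90% joint power needs 75 evaluable per arm at correlation 0 (75/0.8 = 93.75, so 94 randomised per arm, 188 in total) or 70 at correlation 0.8 (70/0.8 = 87.5, so 88 per arm, 176 in total), against the 150 planned. The Trial status section reports 83 recruited with enrolment continuing, so the rule could still be set in advance at that stage.

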**Discussion:**

Integrated traditional Chinese and Western medicine is commonly used for angina in China. This study will evaluate the clinical effectiveness and safety of adding QJHX based on standardized Western medications. The results of the trial will provide high-level clinical research-based evidence for the application of QJHX in MVA.

**Trial registration:**

Chinese Clinical Trial Registry ChiCTR1900027015. Registered on 28 October 2019.

**Supplementary Information:**

The online version contains supplementary material available at 10.1186/s13063-021-05508-x.

## Administrative information

Note: the numbers in curly brackets in this protocol refer to Additional file 1 SPIRIT checklist item numbers. The order of the items has been modified to group similar items (see http://www.equator-network.org/reporting-guidelines/spirit-2013-statement-defining-standard-protocol-items-for-clinical-trials/

## Introduction

### Background

Microvascular angina (MVA) is a clinical syndrome manifested by exertional angina or myocardial ischemia caused by dysfunction of small anterior coronary arteries and small arteries [2]. Currently, the etiology of MVA is thought to be related to coronary microcirculation dysfunction (CMD), coronary endothelial dysfunction, low estrogen levels, and inflammatory response [3]. According to a survey, approximately 112 million people worldwide suffer from angina pectoris [4]. Nearly 70% of patients who underwent coronary angiography showed normal arteries but still had symptoms of myocardial ischemia, and there were more women than men [5]. In a Danish study of 11,223 patients with stable angina who underwent coronary angiography, 32% of men showed non-obstructive coronary artery disease (CAD), compared to 65% of women, and this proportion has been increasing [6]. According to the survey, CMD is the most common type of MVA, and some patients also present with the mixed epicardial and microvascular type of vasospasm caused by epicardial spasm [7]. Currently, statins, angiotensin-converting enzyme inhibitors (ACEIs), and calcium antagonists are the main drugs for the treatment and relief of MVA [2]. However, the results of these drugs have not been uniform in different clinical studies, leading to recurrent disease and poor quality of life in patients [8]. In addition, Western medicine alone is ineffective, and multiple drugs have significant side effects. There is still a need to develop more effective treatments for MVA. In China, a study has confirmed that the combination of Chinese and Western medicines is significantly better than the use of Western medicines alone for the treatment of MVA [9].

According to its manifestations and clinical characteristics, MVA is called “chest pain,” “heartache,” and “true heartache” in traditional Chinese medicine (TCM). Zhang believes that the pathogenesis of thoracic obstruction is the deficiency in origin and excess in superficiality; thus, the reinforcing method is one of the effective methods to treat MVA [10]. Qi-Jing Hui-Xin Decoction (QJHX), a formula for the treatment of angina pectoris, consists of 10 herbs, including *Astragalus propinquus*, *Polygonatum sibiricum*, *Ziziphi spinosae*, and *Panax notoginseng*. The positive clinical efficacy of QJHX for coronary heart disease has been shown in our previous studies that QJHX can reduce angina scores in patients with CAD compared to Western medicine treatment alone. Meanwhile, experimental studies have also confirmed that QJHX can improve cardiac function in rats with myocardial ischemia. In this study, we propose to perform a multicenter randomized controlled clinical study to further observe the clinical efficacy of QJHX intervention in MVA patients and its effect on long-term prognosis.

## Methods/design

### Study design

This study is a multi-center, prospective, randomized controlled trial designed to evaluate the efficacy and safety of QJHX in patients with coronary MVA based on standardized Western treatment. A flow diagram of this study protocol is shown in Fig. 1.

**Fig. 1 Fig1:**
[figure not shown]
Flow diagram of this study protocol

To avoid regional differences, the study will be conducted in three hospitals from different areas of Shanghai. The points of data collection in this trial are as follows: intervention period (12 weeks): baseline, medication for 4 weeks ±3 days, medication for 8 weeks ±3 days, medication for 12 weeks ±3 days for hospital visits, and telephone follow-up for 12 weeks ±7 days after the end of the intervention. The corresponding items will be measured according to the time point of data collection. The detailed information is shown in Fig. 2.

**Fig. 2 Fig2:**
[figure not shown]
Study schedule of enrolment, interventions, and assessments. QJHX, Qi-Jing Hui-Xin Decoction; CCS, Canadian Cardiovascular Society; TCM, traditional Chinese medicine; SAQ, Seattle angina questionnaire; EKG, electrocardiogram; MACE, major adverse cardiac events

### Sample size

According to the results of a previous single-center clinical observation, after 12 weeks of treatment with QJHX, the effective rate was 85.7% in the treatment group and 60.1% in the control group. According to the sample calculation decoction, the number of samples is *n* = 61 cases in each group. In the decoction, *p*_*1*_ and *p*_*2*_ are the estimated values of the two population rates, respectively, *p* is the combined rate, *p* = (*p*_*1*_ + *p*_*2*_)/2, when *α* = 0.05, *β* = 0.10, *u*_α_ = 1.96, and *u*_β_ = 1.282 in the double test and bilateral test. The sample size was 75 cases in each group, a total of 150 cases, taking into account a 20% drop-off rate.
$$ {\mathrm{n}}_1={n}_2{\frac{\left[ ua\sqrt{2p\left(1-p\right)}+ u\beta \sqrt{p_1\left(1-{p}_1\right)+{p}_2\left(1-{p}_2\right)}\right]}{{\left({p}_1-{p}_2\right)}^2}}^2 $$

### Eligibility criteria

Eligible patients will be those who meet all of the following inclusion criteria and do not have any of the listed exclusion criteria.

### Diagnostic criteria

The diagnostic criteria of primary stable MVA [2, 11]: (1) typical exertional angina symptoms, but nitroglycerin is ineffective. (2) Objective evidence of myocardial ischemia (ST-segment depression, myocardial perfusion defect, or increased myocardial metabolites) under resting or loading conditions, but no segmental ventricular wall motion abnormality. (3) The case fatality ratio (CFR) measured by noninvasive or traumatic imaging technology is < 2.0. (4) There was no obvious subepicardial coronary artery stenosis (< 20%) by coronary angiography or coronary computed tomography. (5) Non-cardiogenic chest pain and other heart diseases are excluded.Microvascular angina pectoris with obstructive CAD: (1) in patients with stable angina pectoris caused by obstructive CAD, such as long-term angina pectoris, severe angina pectoris, and angina pectoris that is readily induced by physical activity, sublingual nitroglycerin is ineffective. (2) The CFR measured by noninvasive or traumatic imaging technology is < 2.0.The angina pectoris severity diagnostic criteria are classified by following the “American College of Cardiology (ACC)/American Heart Association (AHA)/American College of Physicians (ACP-ASIM) Chronic Stable Angina Pectoris Management Guidelines” and “Canadian Cardiovascular Society (CCS) Angina Pectoris Severity Classification.”

### Inclusion criteria

Age over 18 yearsPatients conform to the diagnostic criteria of MVA (CSS angina severity grades I–III)TCM syndrome meet the Guideline for Clinical Study on Angina Pectoris of CHD Treated with Traditional Chinese Medicines and Natural Medicines [12]Sign informed consent and willingness to accept Chinese medicine treatment

### Exclusion criteria

Severe heart disease (unstable angina, severe arrhythmia, and others), chest pain caused by diseases other than CAD, such as psychosis, severe neurosis, hyperthyroidism, biliary heart syndrome, gastroesophageal reflux, and aortic dissectionComplicated with uncontrolled grade III hypertension (systolic blood pressure (> 180 mmHg) and/or diastolic blood pressure (> 110 mmHg), severe cardiopulmonary dysfunction, and severe arrhythmiaThe patients with liver, kidney, hematopoietic system, and other serious diseasesThose who have participated in other drug clinical trials within 1 monthThose who have recently (over 4 weeks) undergone major surgeryPregnancy, lactating women, or pregnant plannersAnaphylaxis or allergic reaction to the test drug ingredients

### Randomization and concealment

Eligible patients will be randomly assigned to the treatment group or the control group in a 1:1 ratio, using SAS® 9.4 statistical software and a site-stratified, block randomization schedule. Randomized allocation sequence of the trial participants will be sealed in opaque envelopes and kept in a double-locked cabinet in an independent data center. Each participating hospital will have an independent drug administrator responsible for random coding and drug management.

### Interventions

Eligible participants will be randomized to either the test group or the control group. According to the patient’s condition, the following primary treatments will be selected: antiplatelet drugs (such as aspirin), statins, β-blockers, calcium antagonists, and nitrates. Participants in the control group will receive primary treatment, while QJHX plus primary treatment will be applied in the test group.

The TCM decoction is a compound preparation of Chinese herbs, whose ingredients are equivalent to *Astragalus propinquus*, *Polygonatum sibiricum*, *Ziziphi spinosae*, and *Panax notoginseng*; 10 herbals in total, packaged in a unit of 3 g. QJHX will be produced by Jiangyin Tianjiang Pharm Co. Ltd. (approval number AH20160363), Jiangsu, China. Drugs will be packaged and distributed according to the random serial number in the drug distribution center.

The dosage, method, and frequency of administration will be explained to the participants orally and in writing. Participants will be instructed to take one pack (3.0 g) at a time, two times per day for 12 weeks. At each visit, the participants will receive the drugs for the next intervention, and the drugs left over from the previous intervention will be returned. The dose taken and the accordingly calculated medication compliance will be recorded in the CRF. The scheduled treatment time will be 12 weeks unless serious adverse events occur or the patient withdraws from treatment. During the observation period, the basic treatment of coronary heart disease is unchanged, and non-pharmacologic care is permitted. Other Chinese herbal medicines, Chinese patent medicines, and psychiatric medication are prohibited. If angina pectoris occurs, nitroglycerin tablets can be temporarily taken. Any combination of medications and doses for physical conditions will be recorded in detail. Any questions raised by participants will be answered to facilitate the completion of the trial. The detailed study schedule is shown in Fig. 2.

